#### TMS-EEG: DLPFC activity

To investigate the acute effects of TBS on the DLPFC activity, TEPs captured with electroencephalography (EEG; i.e., TMS-EEG), will be collected before and after the first and last TBS session of the initial treatment phase (i.e., session 1 and session 20 for remitters, or session 30 for individuals receiving an additional 2 weeks of treatment), and before and after the last treatment session of the maintenance phase. This will be done to investigate treatment-induced long-term changes of TBS induced-plasticity in both DLPFCs. A TMS-compatible 64-channel EEG cap (ActiCap Slim, Brainvision, Gmb) will be positioned on participant's head. Conductive gel will be inserted in each electrode on the EEG cap using a syringe. Impedance levels will be kept under 5 kΩ. An ActiCHamp Plus EEG system and Brain Vision Recorder software (BrainVision, Gmb) will record EEG signals at a sampling rate of 5000 Hz. Electrodes will be referenced online to CPz and grounded to FPz. To minimize TMS-induced artefacts, EEG wires will be arranged prior to recordings according to Sekiguchi et al. 2011 [98]. To minimize auditory and somatosensory potentials, a white noise which includes specific time-varying frequencies of the TMS click will be delivered through sound-reducing earbuds during EEG recordings and sound-reducing ear defenders will be positioned on top of the earbuds, as recommended by Rocchi et al. 2021 [99]. To reduce coil vibration to the skin, a thin layer of foam will be placed under the coil. Finally, a questionnaire assessing the level of sensory perception using a Likert scale (i.e., sound, vibration, muscle contraction) will be administered after each TMS-EEG session.

RMT and AMT will be re-investigated after the placement of the EEG cap due to the added distance to the scalp. Participants will be asked to close their eyes and a four-minute resting EEG will be recorded. Next, pre and immediately post the participant's regular TBS treatment, a block of 80 single-pulse TMS at a stimulation intensity of 120% of RMT will be delivered over the left and right DLPFC and TEPs will be recorded.

EEG data will be analyzed using custom scripts on Matlab platform (R2021, Mathworks, USA) and toolboxes including EEGLAB [100] and Fieldtrip [101]. The signal will be epoched around the TMS pulse and baseline corrected to TMS free data. Surrounding TMS pulse signal will be removed and interpolated. Noisy channels and epochs will be removed via an automated script [102]. Two rounds of independent component analysis (ICA) will be performed with EEGLAB *fastica* algorithm to remove the TMS-related artefacts (i.e., ICA1: high amplitude activation removal) and other sources of artifacts (i.e., ICA2: eye movements, eye blinks, muscle activation, and other TMS-related artifacts removal). Bandpass and notch filters will be applied. Removed channels will be interpolated and data will be re-referenced to the average scalp electrodes. TEPs will be measured at the location of stimulation and on a whole-brain basis and amplitudes of TEPs will be compared across time at the typical time windows (N15, P30, N45, P60, N100, and P200). TMS-evoked oscillatory power, namely event related spectral perturbation (ERSP), will be measured by converting TEPs into the frequency domains using Morlet wavelet decomposition, and power values will be averaged in the delta to gamma frequency bands at the typical time windows. TBS-induced DLPFC activity changes will be determined by the pre-post differences in amplitude of TEPs and power of TMS-evoked cortical oscillations over the left and right DLPFC. See Table 4 for a full list of TMS and neuroimaging techniques used in the study, their purpose/proposed neurophysiology, targeted CNS structure, and primary reason for collecting.

## Data analysis

All statistical tests will be two-tailed, and significance (*p*-value) will be set at α = 0.05. All analyses will be performed on SPSS (Chicago, US) and/or using the open-source R statistical software (R core Team, Vienna, Austria and the R-Studio package rstatix; Kassambara, 2022). All data will be reported descriptively to summarize population characteristics. Unless otherwise stated, continuous data will be reported as mean and standard deviation (mean ± SD) and dichotomous variables will be reported as frequency (i.e., percentage) values.

All participants will be included in the analyses ‘as-randomized’ (i.e., bilateral and unilateral TBS) and data will be analyzed regardless treatment adherence and drop-outs. To this end, missing values in the data set (due to participants missing appointments, drop-out/discharge), if present, will be appropriately managed during analysis as per previous suggested procedures for clinical research [103, 104].

### Data management

Except for the screening forms, the consent forms and the master code list, all data will be identified exclusively by an anonymous identification code. This code will be attributed following the phone screening, prior to the first visit. Following this, all documents will contain only de-identified/anonymous data. Paper copy of the Informed Consent Forms will be kept in a locked filing cabinet under the responsibility of the Principal Investigator (ST). The Research Electronic Data Capture (REDCap; https://www.project-redcap.org/) will be used for clinical data collection and overall study data management over the course of this project. Participant interview and self-report data will be entered directly in a case report form (CRF) using the REDCap [105] and secured by multiple levels of authentication. Administrative privileges will be given to a Data Manager who will be responsible for design of CRFs, data entry management and quality control. All data will be password-protected and saved in a secured server. These will include the EEG and TMS raw data, master randomization list, the subject identification code list and the subject enrollment list. Automatic backups of electronic data will be performed daily.

To assure double-blinding, the master randomization list will be created by a scientist of the research centre that is not involved in the research project. A paper copy will be kept in a sealed envelope stored in a locked filing cabinet and a password-protected electronic copy will be kept on a flash drive in a sealed envelope stored in a locked filing cabinet.

Qualtrics will only be used as a means to store participant answers to the MINI assessment. This will be conducted on a laptop that is kept in a locked cabinet. Qualtrics uses TLS or Transport Layer Security encryption (also known as HTTPS) for all their data that is transmitted through their platform. Our Qualtrics account is password protected. Qualtric services are hosted by data centres that are trusted as they are audited independently using the SSAE-18 method (an industry standard).

As per the Canada Tri-Council Policy Statement: Ethical Conduct for Research Involving Humans (TCPS-2), a data monitoring committee is not required for this trial. Auditing will be conducted yearly from the principal investigator. The Royal’s Research Ethics Board will also conduct auditing of trial conduct during the course of the trial.

In accordance with our commitment to transparency and the ethical conduct of this clinical trial, a comprehensive plan for disseminating trial results to various stakeholders was established. Firstly, we intend to communicate trial outcomes to participants, ensuring they receive understandable summaries of the study's findings in plain language. Healthcare professionals and researchers will be informed through open-access peer-reviewed publications in relevant medical journals and presentations at local, national, and international conferences. Findings will also be reported in publicly accessible clinicaltrial.gov database.

### Sample size

Based on our power calculations and the findings from exemplary studies, our sample size offers sufficient statistical power for the planned statistical tests. For example, Plewnia et al. (2014), in *n* = 32 (16/group), found clinically meaningful differences in response to treatment rate (≥ 50% reduction in baseline MADRS score) when comparing 6 weeks of bilateral sequential vs sham TBS (56% vs 25%, respectively) [42]. In *n* = 60 (15/group), Li et al. (2014) showed that 2 weeks of bilateral sequential TBS had superior effectiveness in treating depressive symptoms (≥ 50% reduction in baseline HRSD-17 score) when compared to unilateral (iTBS or cTBS) or sham TBS [106]. For our primary (non-inferiority) statistical analysis (i.e., analysis of covariance, ANCOVA), a total sample size of *n* = 158 was calculated [Gpower Software V.3.1 [107]; power 0.80, α = 0.05, expected effect size *Cohen’s f* = 0.25 (medium; Cohen, 1988)]. For our analysis of predictors of response (i.e., regression analysis), a total sample size of *n* = 30–39 will be required for a regression model that includes 3–6 independent (and/or controlling) variables predicting 30% (R^2^) of variance in the outcome (dependent) variable (Gpower Software V.3.1 [107]; power 0.80, α = 0.05, expected effect size *Cohen’s f*^*2*^ = 0.43) [108]. All other statistical tests are exploratory and, therefore, no sample size calculations were performed. Therefore, in order to achieve the calculated sample size (*n* = 158), we aim to recruit a minimum of 171 individuals, considering an anticipated dropout rate of 6–8% based on previous research [37]. Our recruitment efforts will be capped at a maximum of 256 participants, aligning with our capacity to provide TBS treatment over a five-year timeframe.

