### Study objectives

No large-scale study has compared left unilateral versus bilateral sequential TBS for treating symptoms of MDD. The primary aim of this naturalistic, randomized double-blinded non-inferiority trial is to investigate the efficacy of unilateral (i.e., iTBS to the left DLPFC) and bilateral sequential (i.e., cTBS to the right DLPFC combined with iTBS to the left DLPFC) on reducing clinical symptoms of MDD. Based on previous research, we hypothesize that both treatments will effectively decrease depressive symptoms to a comparable degree (i.e., non-inferior) [33, 34, 61]. The incorporation of covariates during analysis may reveal a superiority of bilateral sequential TBS over unilateral treatment in specific subgroups. These subgroups include older individuals (≥ 60 years-old; [62], and/or individuals presenting with comorbid anxiety, and post-traumatic stress disorder [33, 63]). As mentioned, the clinical efficacy of rTMS is time limited [57, 58]. Therefore, this study will also investigate the efficacy of a six-month flexible maintenance phase. Additionally, to better understand the TBS-induced neurophysiological changes and their associations with therapeutic responses, multiple objectively measured neurophysiological variables will be assessed in this study. See Table 1 for a brief description of outcome measures and detailed hypotheses of this study. Ultimately, this study aims to: 1) inform whether unilateral TBS performed over the DLPFC is non-inferior to bilateral sequential TBS on treating MDD, 2) provide insight on neurophysiological mechanisms associated with treatment-induced effects and their longitudinal changes resulting from treatment, thus providing biomarkers of treatment response, and 3) explore neurophysiological markers, demographics, and clinical characteristics that may help identify responders and non-responders to treatment, paving the way for a more refined and personalized approach to TBS treatment.

**Table 1 Tab1:** Outcomes and hypotheses of the study

Outcome	Rationale	Hypothesis
Clinical (primary)	Investigate changes in severity of depressive symptoms	Unilateral TBS will be non-inferior in comparison to bilateral sequential TBS on reducing depressive symptoms

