## Methods

### Study design and overview

This is a double-blinded randomized, naturalistic, non-inferiority trial comparing unilateral vs bilateral sequential TBS (iTBS in the left vs cTBS in the right followed by iTBS in the left DLPFC, respectively). Participants enrolling in this study are referred by their physician to receive rTMS for the treatment of MDD and are randomized in a 1:1 ratio to receive either unilateral or bilateral sequential TBS. The study design and timeline of assessments and treatment schedule is presented in detail in Fig. 2.

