### Randomization and blinding

Participants are randomized (1:1 ratio) using the study randomizer software (https//www.studyrandomizer.com). A permutated block is used to randomize participants into the treatment groups. Participant stratification is based on the following variables: 1) age (< 65 or ≥ 65 years-old), 2) depression (unipolar or bipolar), 3) comorbid generalized anxiety (yes or no), 4) comorbid post-traumatic stress disorder (yes or no), and 5) biological sex (male or female). Upon entering these participant characteristics, the software provides a number (e.g., 0 or 1) that corresponds to a treatment group in which experimenters and participants are blinded to. Participants will remain assigned to their designated group until the treatment concludes.

This study is a two-arm double-blind trial as neither the participants nor the outcome assessor, care provider and data analysts will know the condition assigned to the participants. The master randomization list of the treatment blinding will be kept by a scientist of the research centre that is not involved in the project. This can be broken in case of emergency (e.g., severe adverse events such as seizure induced by treatment) and they can then inform required medical professionals directly if necessary. Directly involved research staff will be blinded (including the principal investigator and study psychiatrists).

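### The 158 given for the primary non-inferiority ANCOVA comes from a difference-detecting calculation with no margin and does not follow from its own inputs for two arms, so the stated 80% power is not established

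*Protocol article*

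**What the plan says.** In the protocol article, the Sample size section introduces the figure with "For our primary (non-inferiority) statistical analysis (i.e., analysis of covariance, ANCOVA), a total sample size of" 158, obtained in G*Power. The inputs are "power 0.80, α = 0.05, expected effect size" f, given as "expected effect size *Cohen’s f* = 0.25 (medium" by the usual convention). No margin, SD or assumed true difference is listed. The same section builds the recruitment minimum on 158: "we aim to recruit a minimum of 171 individuals, considering an anticipated dropout rate of 6–8" per cent. It caps recruitment at 256.

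The design is fixed elsewhere:

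- Randomization and blinding: "This study is a two-arm double-blind trial".
- Study design and overview: participants are "randomized in a 1:1 ratio to receive either unilateral or bilateral sequential TBS".
- Non-inferiority analysis: an ANCOVA of final HRSD-17 score with baseline HRSD-17 as covariate.
- Data analysis: "All statistical tests will be two-tailed, and significance (*p*-value) will be set at α = 0.05".
- Study objectives: the hypothesis is that "both treatments will effectively decrease depressive symptoms to a comparable degree (i.e., non-inferior").

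**The concern.** There are two separate faults.

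First, an expected effect of f = 0.25 is the difference that an ordinary ANCOVA F-test is sized to detect. The trial does not expect a difference. The power of a non-inferiority comparison depends on the margin and on the true difference assumed, usually zero, and neither is an input here. The Non-inferiority analysis section has the same confusion, since it makes comparability of the arms the null hypothesis.

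Second, 158 does not look like the G*Power answer for a two-arm design with these inputs.

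This paragraph is the only quantitative justification for the size of the primary comparison, and it sets the recruitment minimum. As printed, a reader cannot tell how large a deficit the trial could rule out with 80% power.

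**Working it through.** **Inputs from the article.** Two arms at 1:1, so 1 numerator degree of freedom for treatment; one covariate; two-sided alpha 0.05; power 0.80; f = 0.25. For two equal arms d = 2f = 0.50 SD.

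**Step 1. Reproduce 158.** The non-central F calculation has non-centrality f²N, numerator df1, and df2 = N − groups − covariates.

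- df1 = 1, two groups, one covariate: N = 128. Non-centrality is 0.0625 × 128 = 8.0, df2 = 125, power 0.801. Entering 0 to 6 covariates leaves N at 128. The normal approximation gives 126.
- df1 = 2: N = 158. With three groups and one covariate, non-centrality is 0.0625 × 158 = 9.875, df2 = 154, power 0.802.
- df1 = 3 gives 179.
- df1 = 1 with other settings: alpha 0.10 gives 101; alpha 0.025 gives 155; power 0.85 gives 146; power 0.90 gives 171. None gives 158, and each contradicts the stated inputs.
- df1 = 1 at N = 158: power 0.878.

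The article's other calculation does reproduce. With f² = 0.43 and 3, 4, 5 and 6 predictors, the regression sizes are 30, 33, 36 and 39, matching the stated 30–39. The mismatch is specific to the ANCOVA figure.

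**Step 2. What 158 gives for non-inferiority.** Take a true difference of 0 and one-sided 0.025, which matches the two-tailed 0.05. With the margin M in units of the baseline-adjusted SD and N analysed in total:

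power = Φ( M / √(4/N) − 1.960 )

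margin for 80% power = (1.960 + 0.842) × √(4/N)

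The article gives no margin, so the margins below are assumptions that show the range.

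| Margin (adjusted SD) | Power at 158 | Power at 256 | N for 80% |
|---|---|---|---|
| 0.25 | 35% | 52% | 504 |
| 0.30 | 47% | 67% | 350 |
| 0.35 | 60% | 80% | 258 |
| 0.40 | 71% | 89% | 198 |
| 0.45 | 81% | 95% | 156 |
| 0.50 | 88% | 98% | 126 |

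Margins at which power is 80%:

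- 158 analysed: 2.802 × √(4/158) = 0.446.
- 256 analysed: 2.802 × √(4/256) = 0.350.
- 236 analysed (256 × 0.92, after 8% dropout): 2.802 × √(4/236) = 0.365.

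**Step 3. Convert to raw SD.** If the baseline-final correlation is r, the adjusted SD is √(1 − r²) times the raw SD. For r = 0.5 (an assumption) the factor is √0.75 = 0.866. The three margins become 0.386, 0.303 and 0.316 raw SD. On that footing, power at 158 for raw-SD margins of 0.30, 0.35 and 0.40 is 59%, 72% and 83%. At 256 it is 79%, 90% and 96%.

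**Step 4. Dropout.** 158/0.94 = 168.1, so 169. 158/0.92 = 171.7, so 172. The stated 171 implies 1 − 158/171 = 7.6%, which is inside the stated 6–8%.

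**The case against.** The strongest reply has four parts.

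**A margin may exist in a document that is not shown.** The analysis is said to follow a cited non-inferiority trial, and an article need not repeat a margin. That is fair, and the absence of a margin from the article is not the point here. But a margin held elsewhere would not change the printed calculation, which rests on an expected difference.

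**The sizes nearly coincide if 0.50 SD is read as a margin.** A one-sided 0.025 non-inferiority test with M = 0.50 SD and a true difference of zero needs 126, against 128 for the two-sided test of f = 0.25. On that reading 158 would give 88% power. This stands as arithmetic, and it is why a reader should not infer that the trial is underpowered. The article nevertheless labels f as an expected effect and not as a margin, so the reading cannot be credited to it.

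**The numerical slip is conservative.** 158 exceeds 128 and costs no superiority power. That is correct, and no reduction to 128 is warranted. It does not rescue the 80% claim, because superiority is not the primary claim.

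**The cause of the slip is unknown.** A reader might infer that a three-group design was entered. Numerator df 2 fits a three-level factor, but the article does not print the df, and df 2 returns 158 whatever number of groups is entered. Only the mismatch is established.

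A reader might also want 171 raised to 172. The article gives a dropout range that yields 169–172, so 171 is consistent with it.

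**Conclusion.** The paragraph is wrong as written. It offers 158 as the size giving 80% power for the primary non-inferiority analysis, but the calculation is for detecting a 0.50 SD difference and contains no margin. The non-inferiority power is therefore not established. It could be well below 80% (35% for a margin of 0.25 adjusted SD) or above it (88% for 0.50), and the article does not say which case applies. Separately, the stated inputs give 128 for two arms. The two-arm superiority power at 158 is 88%, not 80%.

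The reproduction result depends only on figures in the article. The non-inferiority powers assume a true difference of zero, one-sided 0.025 and hypothetical margins in baseline-adjusted SD. The raw-SD versions also assume r = 0.5.

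**What to change.** Replace the f = 0.25 calculation with a non-inferiority one that states the margin, a true difference of zero, one-sided 0.025, the assumed HRSD-17 SD and the assumed baseline-final correlation. Then say what the existing sizes deliver:

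- 158 analysed: 80% power for a margin of about 0.45 baseline-adjusted SD (0.39 raw SD if r = 0.5).
- 256 analysed: about 0.35 (0.30), or about 0.36 (0.32) if 236 remain after 8% dropout.

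If the margin is smaller than these, give the actual power at 158 and at the cap. If f = 0.25 is kept as a superiority statement, give its power at 158 as 88%. Leave 158, the minimum of 171 and the cap of 256 unchanged.

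The cost is one rewritten paragraph and no recruitment beyond the existing cap. The downside is that the stated power may look less favourable.

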### Non-inferiority analysis – unilateral vs bilateral sequential TBS

As per Blumberger, et al. (2018), a non-inferiority analysis will be performed to investigate whether the proposed bilateral sequential TBS is non-inferior to the current FDA-approved unilateral iTBS [37]. An ANCOVA will be performed with the baseline HRSD-17 as controlling (i.e., covariate) and the final HRSD-17 score as the dependent outcome variable. The null hypothesis is that the baseline-adjusted final HRSD-17 scores for unilateral and bilateral stimulation will be comparable (i.e., non-inferior) [33, 34, 61]. Although, the incorporation of covariates (i.e., older individuals and individuals presenting with comorbid anxiety and/or post-traumatic stress disorder) during analysis may reveal a superiority of bilateral sequential TBS over unilateral treatment. During ANCOVA, potential missing data will be addressed using multiple imputation methods [104].

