**Methods:**

In this naturalistic, randomized double-blinded non-inferiority trial, participants with a major depressive episode will be randomized to receive either unilateral (i.e., continuous TBS [cTBS] to the right and sham TBS to the left DLPFC) or bilateral sequential TBS (i.e., cTBS to the right and intermittent TBS [iTBS] to the left DLPFC) delivered 5 days a week for 4–6 weeks. Responders will move onto a 6-month flexible maintenance phase where TBS treatment will be delivered at a decreasing frequency depending on degree of symptom mitigation. Several clinical assessments and neuroimaging and neurophysiological biomarkers will be collected to investigate treatment response and potential associated biomarkers. A non-inferiority analysis will investigate whether bilateral sequential TBS is non-inferior to unilateral TBS and regression analyses will investigate biomarkers of treatment response. We expect to recruit a maximal of 256 participants. This trial is approved by the Research Ethics Board of The Royal's Institute of Mental Health Research (REB# 2,019,071) and will follow the Declaration of Helsinki. Findings will be published in peer-reviewed journals.

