### Unilateral and bilateral treatment – iTBS and cTBS

The TBS parameters used in this study are consistent with previous determined guidelines [90]. Specifically, TBS will consist of triple-pulse 50-Hz bursts applied at a rate of 5 Hz using a MagPro X100-MagOption stimulator device (Magventure, Farum, Denmark). iTBS will be delivered through a B70 coil and cTBS will be delivered using an active/sham B65 figure-of-eight cooled-coil (Magventure, Farum, Denmark). Unilateral TBS consists of 40 s of sham cTBS applied to the right DLPFC followed by 190 s of iTBS (i.e., excitatory-inducing) over the left DLPFC. Bilateral sequential TBS will consist of 40 s of cTBS (i.e., inhibitory inducing) over the right DLPFC followed by 190 s of iTBS over the left DLPFC. Stimulation intensity for both iTBS and cTBS will be 80% of the individual's active motor threshold (AMT) assessed with single-pulse TMS (for AMT protocol, see *Single- and Paired-Pulse TMS* section below). Magnetic resonance imaging (MRI) -assisted neuronavigation will ensure proper coil position and targeting of the participants’ DLPFC. The TMS coil will be positioned with the handle pointing backwards and at a 45-degree angle from the midline and centered against the left and right DLPFC locations (e.g., Fig. 1). The DLPFC stereotactic coordinates (MNI-152) are: x = -38, y = 44, z = 26 [37].

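### The primary non-inferiority hypothesis is stated in both directions: bilateral against unilateral in the abstract and analysis section, unilateral against bilateral in the objectives and Table 1

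*Protocol article*

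**What the plan says.** Four places in the protocol article name a test arm and a reference arm, and they split two against two.

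- **Bilateral is the test arm, unilateral the reference.** The abstract (Methods) says the analysis will examine "whether bilateral sequential TBS is non-inferior to unilateral TBS". The section on the non-inferiority analysis asks "whether the proposed bilateral sequential TBS is non-inferior to the current FDA-approved unilateral iTBS".
- **Unilateral is the test arm, bilateral the reference.** Aim 1 under Study objectives is to "inform whether unilateral TBS performed over the DLPFC is non-inferior to bilateral sequential TBS on treating MDD". The primary clinical row of Table 1 reads: "Unilateral TBS will be non-inferior in comparison to bilateral sequential TBS on reducing depressive symptoms".

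Three other statements bear on the primary comparison without naming a direction. The analysis section says "The null hypothesis is that the baseline-adjusted final HRSD-17 scores for unilateral and bilateral stimulation will be comparable (i.e., non-inferior". The opening of Data analysis makes every test two-tailed at 0.05. The Sample size section uses Cohen's f = 0.25, which has no sign.

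The unilateral arm itself is also described in two ways. The abstract has "continuous TBS [cTBS] to the right and sham TBS to the left DLPFC". The section on unilateral and bilateral treatment has "Unilateral TBS consists of 40 s of sham cTBS applied to the right DLPFC followed by 190 s of iTBS" over the left side. Study objectives and the study design overview also describe the unilateral arm as left-sided iTBS.

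**The concern.** Non-inferiority is a one-sided claim. Its null is that the test arm is worse than the reference by at least the margin, so exchanging the arms changes the null and changes which confidence limit decides the trial. A null of comparability cannot settle this, because it names no test arm and is not the hypothesis that a non-inferiority test sets out to reject.

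The practical messages differ too. As the treatment section describes the arms, both receive the same left-sided iTBS and differ only in active or sham cTBS on the right. If bilateral is not worse than unilateral, adding right cTBS costs nothing in efficacy. If unilateral is not worse than bilateral, leaving it out costs nothing. One data set can support the first and not the second.

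An asymmetric result is plausible on the article's own evidence. The Sample size section cites a four-arm trial in which bilateral TBS did better than either unilateral form, and both Study objectives and the analysis section allow for bilateral superiority in some subgroups. If the direction stays open, it could be settled after the results are known.

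**Working it through.** **Inputs from the article.** Two arms, 1:1; 158 analysed, so 79 per arm; α = 0.05 two-tailed (each end of a two-sided 95% interval tests one-sided 0.025); power 0.80; f = 0.25; recruitment capped at 256.

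**Assumed inputs.** The margin (0.3 to 0.5 SD) and the true difference d, in SD units, positive when bilateral is better. No gain from the baseline covariate unless stated.

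**1. Does the sample size reveal a direction?** For two equal arms, f = 0.25 is a standardised difference of 0.5. A noncentral F calculation for a two-arm ANCOVA (numerator df 1) gives a total of 128, not 158; 158 appears with numerator df 2. Either way this is power to detect an unsigned difference, so the sample size does not settle which arm is the reference.

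**2. How one interval can give two verdicts.** The standard error is √(2/79) = 0.159 SD, so the 95% half-width is 1.96 × 0.159 = 0.312 SD. Take a margin of 0.4 SD.

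- Observed difference 0: the interval is −0.31 to 0.31. Both limits are inside ±0.4, so both versions are met.
- Observed bilateral benefit 0.2: the interval is −0.11 to 0.51. The lower limit is above −0.4, so bilateral is non-inferior. The upper limit exceeds 0.4, so unilateral non-inferiority is not shown.

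**3. How often the verdicts separate.** With Φ the standard normal distribution function and m the margin:

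- P(bilateral non-inferior) = Φ((m + d)/0.159 − 1.96)
- P(unilateral non-inferior) = Φ((m − d)/0.159 − 1.96)

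| True bilateral benefit d | Margin m | Bilateral non-inferior | Unilateral non-inferior |
|---|---|---|---|
| 0 | 0.3 | 47% | 47% |
| 0 | 0.4 | 71% | 71% |
| 0 | 0.45 | 81% | 81% |
| 0 | 0.5 | 88% | 88% |
| 0.1 | 0.3 | 71% | 24% |
| 0.1 | 0.4 | 88% | 47% |
| 0.1 | 0.5 | 97% | 71% |
| 0.2 | 0.3 | 88% | 9% |
| 0.2 | 0.4 | 97% | 24% |
| 0.2 | 0.5 | 99% | 47% |

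For m = 0.4 and d = 0.2: (0.6/0.159) − 1.96 = 1.81, giving 97%; (0.2/0.159) − 1.96 = −0.70, giving 24%.

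**4. What direction does to sample size.** Total N = 2 × 2(1.96 + 0.84)²/(m ± d)², with the per-arm number rounded up. At m = 0.5, 80% power and one-sided 0.025:

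- d = 0: 126 in either direction.
- d = 0.1: 88 for bilateral non-inferior, 198 for unilateral non-inferior.
- d = 0.2: 66 and 350. The latter exceeds the cap of 256.

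**5. Sensitivity.** At m = 0.45 and d = 0.2 the two chances are 98% and 35%. If the baseline score correlates 0.5 with the final score (assumed), the standard error falls to 0.159 × √0.75 = 0.138 and the 35% becomes about 44%. With 256 analysed and no adjustment, it is √(2/128) = 0.125 and the 35% becomes about 52%. The gap narrows but remains.

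**The case against.** The best defence is that the one section specifying the primary analysis does state a direction, matches the abstract, and gives a reason: unilateral iTBS is the approved treatment and bilateral the proposed one. That stands. A reader might infer from the conflict that the primary conclusion is undefined; the article does not support that. A direction is written in the analysis section, but it is contradicted by the stated aim and primary hypothesis. If the interval falls inside the margin on both sides, the contradiction has no effect on the verdict. The authors expect comparable arms, so that outcome is possible.

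A reader might also infer that the Table 1 direction should prevail, because it is the stated primary hypothesis and bilateral superiority is anticipated in some subgroups. Neither reason decides it. The first picks one side of the contradiction. The second fits equally well with bilateral as the test arm, where superiority could be examined after non-inferiority; the analysis section mentions possible bilateral superiority in just that context.

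Finally, the analysts are blinded and an analysis plan that is not shown may already fix the direction. Choosing after the results is therefore a risk, not something the article shows will happen. But a separate plan does not remove a contradiction between the published hypothesis and the published analysis.

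**Conclusion.** The point holds as a contradiction on the primary hypothesis: the direction is given both ways, and the symmetric null, the two-tailed rule and the unsigned effect size do not resolve it. It is an error in what the article states, not a detail left to a fuller document.

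Its consequence depends on the truth. At no true difference, direction makes no difference to the chance of success. At a bilateral benefit of 0.2 SD, the probabilities of success in the two directions differ by 52 to 79 percentage points across the assumed margins (99 − 47 = 52 at 0.5 SD; 88 − 9 = 79 at 0.3 SD). These figures rest on assumed margins and true differences, 158 analysed and a normal approximation without covariate adjustment. The exact values would move with those choices; the asymmetry would not disappear.

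The conflicting descriptions of the unilateral arm are a separate, secondary discrepancy. They do not determine the direction, but the reader needs to know what the arm is before either non-inferiority claim has a meaning.

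**What to change.** Before unblinding, the authors should:

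1. Choose one test arm and one reference arm and give the reason. The analysis section offers the approved unilateral iTBS as reference; Table 1 implies the reverse. Either can be defended.
2. State the null as a signed, baseline-adjusted HRSD-17 difference against the margin, and say which confidence limit decides.
3. Use that direction in the abstract, Study objectives, Table 1 and the non-inferiority analysis section.
4. Report the other direction from the same two-sided 95% interval as a labelled secondary result.
5. Reconcile the abstract's description of the unilateral arm with Study objectives, the design overview and the treatment section.

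No new data are needed, but the change is not purely wording. One stated aim becomes secondary. If unilateral becomes the test arm and bilateral is truly better, power is lower, so the sample size should be checked against the chosen direction and margin within the cap of 256.
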